#### Relevance of on-road assessment

3.1.2

- In the event of concordance between opinion following RDA and other assessments (neuropsychological, multiprofessional, approved doctor’s opinion), the assessment tools mentioned can be considered to be good predictors of driving ability, in accordance with the literature (Marshall et al., 2007).- In the event of a discrepancy between RDA and other assessments, the RDA value will remain undeniable, but results can be explored and discussed depending on which assessment there is a discrepancy with, and the direction of this discrepancy. More specifically, a discrepancy between RDA and neuropsychological assessment can highlight coping strategies linked to awareness of cognitive disorders. In fact, correlation between neuropsychological assessment and actual driving may depend on the individual’s level of awareness of their abilities (Griffen et al., 2011). These results would not, therefore, call into question value of the RDA. On the other hand, a discrepancy between the opinion given following RDA and that given by the PRM doctor (multiprofessional evaluation) or the approved doctor may raise questions about value of the RDA, or at least the importance attached to it by doctors (PRM or approved doctor).- In the event of concordance between the TRIP score and the various assessments, TRIP can be considered a relevant tool for predicting driving ability. Conversely, in the event of discrepancies between TRIP and other assessments, the usefulness of this grid can be discussed. Further analysis could highlight the relevance of certain sub-scores.- In the event of concordance between the number of interventions on the controls and professional opinions, this criterion can then be considered to be a good predictor of driving ability. On the other hand, in the event of discrepancies, a certain tolerance may be accepted if the driving instructor intervenes on the controls during RDA.

#### Relevance of multiprofessional evaluation

3.1.3

- Agreement between the multiprofessional opinion and that of the approved doctor will enable the approved doctor to get additional information, in line with this evaluation recommended by the HAS and now mandatory.- A discrepancy between the multiprofessional opinion and that of the approved doctor will help to identify situations for which an opinion is difficult to formulate. Using the scientific evidence gathered, an analysis of advantages and disadvantages can be carried out to shed more light on the fitness to drive evaluation, with a view to helping approved doctors identify the best tools for deliberating their opinions.

### Longitudinal study

3.2

Thanks to the longitudinal study, further analyses will enable us to measure the relevance of the multiprofessional evaluation by comparing each assessment with the road risk. Assessments that are significantly correlated with perceived road risk (as well as with self-reported accident rates) can be considered as good predictors of road risk, further supporting their relevance.

The longitudinal study will also shed light on any changes in driving habits adopted by participants since regularization of their driving license. These analyses will quantify the adoption of coping strategies related to npABI sequelae. Complementary analyses would also enable us to study relationships between changes in driving habits and various assessment scores. For example, a high correlation between changes in driving habits and BIDSAM would highlight the link between metacognition and behavioral regulation (adjusting driving to compensate for cognitive sequelae).

Lastly, this longitudinal study will provide some answers to the HAS recommendation that people with npABI be given the best possible support to resume or stop driving. By questioning participants, the support for resuming driving questionnaire will highlight the self-reported relevance of multiprofessional assessment for:- Judging their driving ability- Becoming aware of their driving ability- Obtaining information and advice from the team- Adjusting their driving (in the case of unrestricted fitness to drive)- Understanding the reasons for unfitness to drive or driving restrictions (in the case of fitness with restriction codes)- Dissuading them from driving (in the event of unfitness)

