#### Longitudinal study

2.2.2

Six and 12 months after deliberation of the approved doctor’s opinion, the study investigators of the rehabilitation centers will send questionnaires to each participant of the cross-sectional study in order to study the road risk prediction performance of the tools and professional opinions. These questionnaires can also be completed with the help of a third party or a therapist. They will aim to gather information about participants’ driving in the 6 and 12 months since the opinion on fitness to drive was delivered. The elements investigated will concern:- aberrant driving behavior with DBQ validated in French (Guého et al., 2014),- possible changes in driving habits with DHQ, based on the Canadian Jerome Driving Questionnaire (JDQ©), and- road risk (accident rate and perceived risk).

Six months after the approved doctor’s opinion, participants will also be asked to complete a questionnaire (support for resuming driving questionnaire) to assess the relevance of multiprofessional educational support aimed at encouraging them to resume driving or dissuading them from doing so. In order to limit participant drop-outs, if they do not respond within one month, a reminder is sent by their SMR referent, with a one-month response period and this procedure will be repeated a second time if no response is received after this deadline. After these two reminders, the SMR referent may also contact the participant by phone to ensure that the e-mails have been received. If the participant refuses or does not reply, the SMR referent sends a final e-mail to the participant to inform them that they will be excluded from the longitudinal study.

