### Analysis

2.3

Participant characteristics and assets will be described and compared. Reasons for refusing to participate will be collected. Descriptive statistics on participant characteristics will be presented. The characteristics of participants included will be compared with those of non-included participants in the eligibility register to ensure their representativeness. Quantitative variables will be described in terms of mean, standard deviation, median, interquartile range and extreme values. Qualitative variables will be described in terms of absolute frequency and percentage per modality. The alpha threshold for statistical significance is set at 5%; 95% confidence intervals will be presented. All the variables collected for people included in the study will be described. Missing data will not be replaced in this study and some participants might be secondary excluded from certain analyses. Sub-group analyses may be carried out, if statistically robust, depending on the number of fitted cars required and the conclusion of the medical examination.

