##### Main criterion: concordance between professional assessments

2.3.1.1

To meet the main objective, the concordance of the results of the neuropsychological assessment, RDA and multiprofessional evaluation will be studied in pairs (agreement between professional assessments). Each professional involved in the study will give a “favorable,” “reserved” or “unfavorable” opinion based on their practice. Evaluation criteria will correspond to cross-tabulated numerical values of results from each assessment tool studied (neuropsychological assessment, RDA and multiprofessional evaluation). “Reserved” opinions indicating driving restrictions will initially be classified as “unfavorable,” so that the results can be expressed as a binary Favorable/Unfavorable variable for each assessment. The RDA results will also include the number of driving instructor interventions on pedals, steering wheel and other car controls, using categorical variables. The values *a*, *b*, *c* and *d* (Table 1) will be used to perform the concordance test detailed in the next section (“Statistical analysis”).

**Table 1 tab1:** Evaluation criterion of the main objective for contingency table.

		Assessment x_i_	
		Favorable	Unfavorable
Assessment x_ii_	Favorable	*a*	*b*
	Unfavorable	*c*	*d*

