#### Longitudinal study (secondary evaluation criteria C to E)

2.3.2

Six and 12 months after deliberation of the approved doctor’s opinion, a longitudinal analysis will enable the following secondary objectives to be met:C. Estimate the road risk prediction performance metrics of each assessment tool (cf. main objective) and of the TRIP, as well as of the approved doctor’s opinion;D. Explore participants’ changes in their driving habits;E. Explore the impact of educational support to encourage or dissuade driving resumption (only explored after 6 months).

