##### Secondary criterion C: road risk performance metrics 6 and 12 months after deliberation of the approved doctor’s opinion

2.3.2.1

The predictive performance indicators of assessment tools, TRIP grid, and approved doctor’s opinion will be estimated in relation to the road risk perceived by participants 6 and 12 months after deliberation of the approved doctor’s opinion (cf. secondary criterion D). The patient will indicate the increase in road risk to road risk according to their perception, in the form of a ternary variable in response to the question “How would you assess your road risk”: (i) lower than before, (ii) identical to before, (iii) higher than before the brain injury. The condition evaluated will be absence of increased road risk perceived by participants 6 and 12 months after the approved doctor’s opinion (negative result), corresponding to the “favorable” modality for assessments carried out in rehabilitation centers (neuropsychological, RDA and multi-professional evaluation) and “fit” for the approved doctor’s opinion (Table 4).

**Table 4 tab4:** Confusion matrix.

		Reality: perceived increased road risk 6 and 12 months after the approved doctor’s opinion has been issued	
		No increased road risk	Increased road risk
Prediction: assessment x_i_	Favorable	Real negative (RN)	False negative (FN)
	Unfavorable	False positive (FP)	Real positive (RP)

The TRIP score will also be analyzed continuously (total adjusted score out of 100), in total and by sub-score.

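### The Discussion awards the label of good road-risk predictor on a significant correlation, although criterion C is defined by sensitivity, specificity and related metrics, and no deciding time point is named

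*Protocol article*

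**What the plan says.** The rule for the conclusion stands in the Discussion, section 3.2 (Longitudinal study): "Assessments that are significantly correlated with perceived road risk (as well as with self-reported accident rates) can be considered as good predictors of road risk".

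The planned analysis stands elsewhere in the protocol article:

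- **Objective.** Section 2.3.2 sets out to estimate the "road risk prediction performance metrics of each assessment tool (cf. main objective) and of the TRIP, as well as of the approved doctor’s opinion". The main objective supplies three tools, whose "concordance of the results of the neuropsychological assessment, RDA and multiprofessional evaluation will be studied in pairs". With the TRIP and the approved doctor's opinion, that makes five assessments.
- **Outcome and timing.** Section 2.3.2.1 says that the indicators will be "estimated in relation to the road risk perceived by participants 6 and 12 months after deliberation of the approved doctor’s opinion". Table 4 has one heading for the true state, and it covers both time points.
- **Metrics.** Section 2.3.3 gives formulas for accuracy, sensitivity, specificity, PPV and NPV, all from Table 4. It names no significance test for criterion C.
- **Error level.** Section 2.3 states: "The alpha threshold for statistical significance is set at 5%; 95% confidence intervals will be presented". The article mentions no multiplicity adjustment.
- **Second outcome.** Section 2.2.2 collects accident rate as well as perceived risk. Accident rate comes back only in the parenthesis in section 3.2.
- **Status.** Sections 2.1 and 2.4 call the study exploratory.

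**The concern.** The Method and the Discussion answer different questions. The Method asks how well each assessment sorts participants into those who do and do not perceive an increased risk. The Discussion awards the label on whether a correlation differs from zero. An assessment can pass the second test and still classify poorly.

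The rule is also open on two points that affect its error rate. It does not say which of the two time points decides. Its phrase linking perceived risk to accident rates can mean that either outcome will do, that both are needed, or that accident rates are only supportive.

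What is at stake is the longitudinal conclusion on each assessment. Section 3.2 uses it to support the relevance of the assessments, and section 3.4.2 hopes that the results can inform the training of approved doctors and clarify the decree. A weak or chance association could be carried forward as evidence of good prediction.

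**Working it through.** The article states no false-positive rate for this rule, so there is no figure to reproduce.

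**Inputs from the article:** 5 assessments (sections 2.3.1.1 and 2.3.2), 2 time points (2.3.2.1), perceived risk as the criterion C outcome (2.3.2.1), accident rate as a second collected outcome (2.2.2 and 3.2), 5% per test (2.3), 100 participants (2.1).

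**Inputs assumed, because the article gives none:** correlation between test statistics of 0 to 0.9 across assessments, 0 to 0.9 across time points and 0 to 0.5 across outcomes.

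**Step 1: independent tests.** The chance of at least one false positive among m tests is 1 − 0.95^m.

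- 5 tests (one time point, one outcome): 1 − 0.95^5 = 22.6%
- 10 tests (5 × 2 time points, perceived risk): 1 − 0.95^10 = 40.1%
- 20 tests (5 × 2 × 2 outcomes): 1 − 0.95^20 = 64.2%
- 10 pairs in which both outcomes must be significant at the same time point: 1 − (1 − 0.05²)^10 = 2.5%

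**Step 2: correlated tests.** Two-sided z-tests with no true association were simulated 100,000 times per setting. The correlation matrix was the product of the three structures above.

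| Correlation: assessments / times / outcomes | Perceived risk only, any of 10 | Either outcome, any of 20 | Both outcomes, same time point | Both outcomes, any time point |
|---|---|---|---|---|
| 0 / 0 / 0 | 40% | 64% | 2.4% | 4.6% |
| 0 / 0 / 0.5 | 40% | 61% | 9.0% | 10.6% |
| 0.5 / 0.5 / 0.3 | 31% | 51% | 4.2% | 5.4% |
| 0.7 / 0.7 / 0.3 | 24% | 41% | 3.4% | 4.1% |
| 0.9 / 0.9 / 0 | 14% | 26% | 1.1% | 1.4% |
| 0.9 / 0.9 / 0.5 | 14% | 24% | 3.4% | 3.5% |

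Over the whole grid the ranges are 14% to 40%, 24% to 64%, and about 1% to 11% for the two readings that require both outcomes. The 15 TRIP sub-scores are not counted. Under the any-result readings they would add to the totals.

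**Step 3: what significance shows.** For a Pearson correlation the critical value is r = t / √(t² + n − 2). With n = 100 and t = 1.984 on 98 degrees of freedom, r = 1.984 / √(3.938 + 98) = 0.197. The square is 0.039, so an assessment that explains about 4% of the variance passes. Perceived risk has three categories and the opinions are binary, so this is an approximation. With non-response the threshold would be somewhat higher.

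**Step 4: side by side.** Sections 2.3.2.1 and 2.3.3 yield sensitivity and specificity for each assessment. Section 3.2 does not use them in its rule.

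**The case against.** The best defence is that criterion C is an estimation exercise. The Method specifies performance metrics, section 2.3 promises 95% confidence intervals, and the significance wording is one sentence in the Discussion. This is right about the plan, and it makes the fix easy. It does not remove the fault, because that sentence is where the article says what will earn the label.

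Several stronger readings are tempting, and the article does not support them:

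- **That no outcome takes precedence, so 20 tests compete.** Section 2.3.2.1 and Table 4 tie criterion C to perceived road risk. Only the time point is left without a decision.
- **That about two in five null studies would declare a predictor.** That figure needs a particular assumption. It is the 10-test result under independence, or the 20-test result at correlations near 0.7 / 0.7 / 0.3. The article gives no correlations. Its design points to dependence: the multiprofessional opinion draws on the other assessments, the RDA opinion and the TRIP come from the same drive, and the approved doctor receives the multiprofessional report. The independence figures are therefore upper ends.
- **That any significant result certainly suffices.** The sentence may require both outcomes, and the rate is then about 1% to 11%.
- **That missing adjustment is itself an error.** The study is declared exploratory, C is a secondary criterion, and multiplicity handling may stand in an analysis plan that is not shown.
- **That differing results at 6 and 12 months are a defect.** They are two legitimate quantities. The gap is only that nothing says which one carries the label.

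The policy use is also conditional on the results, and section 3.4.1 foresees randomized trials to verify the assessments.

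**Conclusion.** The point holds as a mismatch between the stated conclusion and the planned metrics, made worse by an open time point and an ambiguous role for accident rates. On perceived risk alone, with any significant result sufficient, the chance of at least one false predictor is roughly 14% to 40%. If accident rates are an alternative route it is about 24% to 64%, and if both outcomes are required about 1% to 11%. These ranges rest on assumed correlations and on no assessment having a true association.

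The mismatch itself does not depend on them. At 100 participants a correlation of about 0.20 is significant, which falls well short of showing good prediction. The exploratory status limits the weight of the multiplicity argument, but it does not make significance a measure of predictive performance. The change is worth making, in proportion to a secondary objective.

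**What to change.** 1. In section 3.2, base the good-predictor statement on the sensitivity and specificity already planned, with their 95% confidence intervals, against perceived road risk.
2. In section 2.3.2.1, name in advance the one time point that decides. Use it in Table 4, and report the other time point as exploratory.
3. State whether self-reported accident rates are supportive or also required.
4. Label the TRIP sub-score analyses against road risk as exploratory.

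Holm adjustment over the five assessments is optional in a declared exploratory study. If the label stayed tied to significance, naming one time point and one outcome would still leave 22.6% for five independent unadjusted tests. Testing each at 0.01 (Bonferroni) would give 1 − 0.99^5 = 4.9%.

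The cost is wording only, with no new data. The downside is that fewer assessments may earn the label.

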### PREVAC study limits

3.3

Brain injury criteria are not controlled in the study, lesion location, severity and extent were not identified, suggesting heterogeneous clinical profiles. In addition, the temporal distance of the lesion was collected but not delimited. Although cognitive sequelae may persist for many years after brain injury, they tend to diminish over time. What’s more, the temporal distance of the lesion favors the development of compensatory strategies.

These factors generate a diversity of cognitive-behavioral profiles that contribute to a lack of homogeneity in the population studied, complicating interpretation of the results. It could be difficult to identify the profiles most likely to resume driving, and the study’s conclusions would then not be applicable to the population as a whole. Secondary analysis with subgroup studies will be conducted to measure differences linked to the temporal distance of the lesion.

### PREVAC study outlooks

3.4

#### Standardizing professional practices

3.4.1

Based on conclusive results of this study, a parallel action-research project is being carried out at regional level, with the aim of standardizing real-life practices and make it easier to write pluriprofessional advice. Based on focus groups conducted within rehabilitation centers, the cross-sectional study protocol will be improved to meet everyone’s interests. These regional outlooks can then be extended to the rest of French metropolitan and even overseas departments.

This study could also pave the way for future research using randomized controlled trials to verify the relevance of the assessments and tools. For example, in order to highlight the value of neuropsychological and on-road assessments (currently not required by law), it might be interesting to compare the road risk of a group of patients who have undergone these assessments, versus a group of patients who have only undergone a sensory-motor and medical assessment.

#### Public policy support

3.4.2

Since the publication of the decree of March 28, 2022, people with npABI have been required to undergo a multiprofessional evaluation, so that the approved doctor can issue an informed opinion on their driving ability. In the context of these recent regulations, this multicenter study presents an opportunity to support public policy by shedding new light on the French Road Safety Delegation (Délégation à la Sécurité Routière, DSR).

Axis 2 of the July 17, 2023 of the CISR aims to ‘better detect, assess and monitor unfitness to drive’. More specifically, the seventh measure raised by this committee is to improve the medical examination of fitness to drive. This measure focuses on reinforcing specialized technical platforms to better assess the medical fitness to drive of patients with cognitive and neuromotor disorders. In this context, depending on the results obtained, this study could clarify the value of the multiprofessional assessment for the approved doctor. It would provide scientific evidence to support the consideration of various assessments carried out in current practice. In particular, as neuropsychological assessment is not included in the decree, this study aims to take better account of invisible disabilities during fitness to drive medical examinations. To achieve this, we hope to identify the best-performing tools that are the most predictive of actual driving ability, considering drivers’ ability to compensate for their cognitive disorders.

The CISR also recommended a measure to reinforce the training of approved doctors in terms of the medical content of their examinations. The operational outcomes of this study will consist in disseminating its conclusive results to professionals concerned by this fitness to drive medical examination. Documentation can be produced for use by teams at rehabilitation centers and approved doctors. With the financial support of the DSR, which funds the PREVAC project, key elements of the study could be integrated into the training of approved doctors, and could clarify the decree of March 28, 2022.
